**Trial design and methods:**

Prospective randomized open multicenter phase III trial including patients with 11–40-mm papillary thyroid carcinoma (Bethesda VI) or suspicious cytology (Bethesda V) confirmed malignant on intra-operative frozen section analysis, with no suspicious lymph nodes on a specialized preoperative ultrasound examination. Patients will be randomized 1:1 into two groups: the reference group total thyroidectomy with bilateral prophylactic central neck dissection, and the comparator group total thyroidectomy alone. All patients will receive an ablative dose of 30mCi of radioactive iodine (RAI) within 4 months of surgery. The primary outcome is to compare the rate of excellent response at 1 year after surgery between the groups, as defined by an unstimulated serum thyroglobulin (Tg) level ≤ 0.2 ng/mL with no anti-Tg antibodies, an normal neck ultrasound and no ectopic uptake on the post-RAI scintiscan. Non-inferiority will be demonstrated if the rate of patients with excellent response at 1 year after randomization does not differ by more than 5%. Setting the significance level at 0.025 (one-sided) and a power of 80% requires a sample size of 598 patients (299 per group). Secondary outcomes are to compare Tg levels at 8 +/− 2 postoperative weeks, before RAI ablation, the rate of excellent response at 3 and 5 years, the rate of other responses at 1, 3, and 5 years (biochemical incomplete, indeterminate, and structurally incomplete responses), complications, quality of life, and cost-utility.

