### Intervention description

#### Randomization of patients

*Pre-registration (inclusion)* of eligible patients after signed informed consent.Surgery must be performed within 4 months of pre-registration.Quality of life (SF-36, EQ-5D, STAI) questionnaires will be completed by the patient within 1 month before the surgery.Before surgery, the patients will first be pre-registered (included) to check that the thyroid nodule is classified cT1bT2N0 and the FNAB cytology is classified type 5 or 6 according Bethesda (Appendix 2).Randomization (and validation of the inclusion)

Randomization (and validation of the inclusion) will then be performed:Before surgery for patients with malignant cytology (Bethesda 6)OR in the operating room, after total thyroidectomy without any particular dissection of paratracheal spaces and after confirmation of malignancy by intra-operative frozen section analysis for patients with suspicious cytology (Bethesda 5).

For patients with a nodule Bethesda 5, the randomization form will incude a confirmation of malignancy of the intra-operative frozen section analysis for patients with suspicious cytology Figs. 1 and 2.

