#### Treatments

##### Baseline assessment

Inclusion and non-inclusion criteria and patient consentNeck ultrasoundLaryngoscopySerum calciumEQ-5D 3 Levels (Annex 2) [48]Quality of life (SF-36) (Annex 3) [47]Anxiety (State-Trait Anxiety Inventory) (Annex 4) [49]Subjective dysphonia and dysphagia (measured via the Voice Handicap Index (ANNEX 5) [45] and SWAL-QOL) (Annex 6)[46]

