## Assignment of interventions: allocation

### Sequence generation

Patients will be prospectively included in the study in 2 steps:Patients will first be registered, after check of eligibility criteria and signature of the informed consent form, before any trial related procedure.Randomization (and validation of the inclusion) will then be performed: (1) before surgery for patients with malignant cytology (Bethesda 6) or (2) in the operating room, after total thyroidectomy and after confirmation of malignancy by intra-operative frozen section analysis for patients with suspicious cytology (Bethesda 5). Randomization will be performed online or by fax with the Trial Master program.

Randomization will be performed online or by fax with the Trial Master program. Patients will be randomly allocated to one of the two treatment groups, based on blocks of participants, stratified by tumor size (cT1b vs cT2) and site (to ensure a balance between the treatment groups at each site). The blocking and stratification measures will not be revealed to those enrolling patients or those allocating the interventions.

Once randomized, patients must be treated as defined in the assigned group and cannot change.

Inclusion/registration and randomization will be performed online or by fax, using the TrialMaster program, and electronically centralized by the Biostatistics and Epidemiology Unit at Gustave Roussy. A fax or an internet access in the operating room or at proximity is then mandatory. In case of any kind of problem, the investigator will contact the study data manager.

The data manager email address, phone, and fax number will be notified in the CRF. In case of any emergency or in the absence of the study data manager, an on-duty data manager will available.

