### Statistical methods

#### Statistical methods for primary and secondary outcomes

Descriptive summary statistics will be provided for continuous demographic, laboratory, and clinical variables. The descriptive summary statistics will include number of patients, means and standard deviations for quantitative variables, and percentages for qualitative data.

Subject demographic and baseline characteristics will be summarized by treatment group. The Student test will be used for the continuous variables (or non-parametric test if variables are not normally distributed), and the chi-square test will be used for the categorical variables.

Primary outcomes s1

The main endpoint will be analyzed 1 year after randomization of the last patient, once all the CRF will have been collected and the database has been cleaned. The analysis will be performed when all patients will have 1 year of follow-up, and no lost of follow-up will be tolerated.

A patient will be in remission if the requirements are met at 1 year following randomization. Conversely, a patient will be considered to not be in remission if the criteria are not met at 1 year following randomization. In the absence of censored data, the proportion of patients in complete remission will be calculated as a percentage.

Since the study is designed as a non-inferiority study, the primary analysis will be carried out by considering all evaluable patients (per-protocol population), as this is the most conservative approach in this context. Patient will be considered as evaluable if the treatment and the follow-up conform to the study protocol (diagnostic tests performed) and if the patient does not have detectable anti-Tg antibodies. A sensitivity analysis using the intent-to-treat (ITT) population, considering all patients in their initial group of randomization, will also be performed, to test the robustness of the results.

The observed difference in patients in complete remission (∆) and its 95% unilateral confidence interval will be calculated. If the unilateral confidence interval does not include the −5% clinically relevant difference (∆L), then the TT alone strategy will be considered as non-inferior to the TT + PCND strategy.

All statistical analyses will be performed using the SAS® software.

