Secondary outcomes s1Unstimulated thyroglobulin levels between groups will be compared between groups using a chi-square test.The rate of patients in complete remission at 3 and 5 years will be compared between groups using a chi-square test.The rate of patients in with structural incomplete response, biological incomplete response, indeterminate response, distant metastases, or further treatments at 1, 3, and 5 years will be compared between the 2 groups using a chi-square test for each type of response.

For these secondary criteria we expect, based on retrospective series comparing the two surgical techniques (total thyroidectomy alone or total thyroidectomy + PND), rates of incomplete response or re-treatement in the range of the following:Difference in locoregional control = 6.9% at 10 years [1]Difference in rate of recurrence = 4.6% at 3 years [2]Difference in rate of retreatment = 8.2% at 5 years [3]Rate of structural recurrence = 1.4% at 8 years [44]The rate of patients at 1 year with persistent hypoparathyroidism requiring medication and/or with persistent vocal fold paralysis will be compared between groups using a chi-square test; subjective dysphonia (Voice Handicap Index) and subjective dysphagia (SWAL-QOL) toxicities will be compared using a Student test for each time of evaluation (or a Kruskall-Wallis non-parametric test if they are not normally distributed).Quality of life and anxiety: The investigator will inform the patient on the objective of QoL data collection. QoL data may be not exploitable in case of great number of missing questionnaires. Data will be analyzed according to the scoring manual of each questionnaire. A longitudinal analysis using a mixed model will be used to take into account of repeated QoL assessment and the initial value. If this analysis shows a significantly different effect between groups or an interaction between treatment and time, an analysis of the treatment effect on quality of life will be carried out at each time. Mean sub-scale scores will be compared using a Student test for each time of evaluation (or a Kruskall-Wallis non-parametric test if they are not normally distributed).

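### Voice and swallowing scores are to be compared without their baseline values, although baseline scores are planned and the quality-of-life analysis uses them; the test is valid but inefficient.

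*Protocol article*

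**What the plan says.** All references are to the protocol article.

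- **Analysis of voice and swallowing.** Under Statistical methods for primary and secondary outcomes, subjective dysphonia (VHI) and dysphagia (SWAL-QOL) "toxicities will be compared using a Student test for each time of evaluation". Kruskal-Wallis is the fallback for non-normal scores. No baseline value or other covariate is named.
- **Analysis of quality of life and anxiety.** The next item in that section reads: "A longitudinal analysis using a mixed model will be used to take into account of repeated QoL assessment and the initial value". Tests at single time points follow only if that model shows an arm effect or an arm-by-time interaction.
- **Baseline collection.** Baseline assessment lists "Subjective dysphonia and dysphagia (measured via the Voice Handicap Index", followed by SWAL-QOL. Randomization of patients gives a shorter list: "Quality of life (SF-36, EQ-5D, STAI) questionnaires will be completed by the patient within 1 month before the surgery". VHI and SWAL-QOL are not in it.
- **Follow-up collection.** Follow-up schedules SWAL-QOL at about 8 weeks. Both scores are listed at 1 year and again in the list for 1, 3 and 5 years. The section on functional secondary criteria mentions them at 1 year only.
- **Primary endpoint.** Sequence generation says randomisation is "stratified by tumor size (cT1b vs cT2) and site". For the primary outcome, the observed difference and "its 95% unilateral confidence interval will be calculated", with no stratum named.

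**The concern.** A baseline score on the same questionnaire usually explains part of the follow-up score. If it is collected and left out, the comparison has a larger standard error than the data require, so a real difference in voice or swallowing is easier to miss. The article sees the value of baseline for the other questionnaires, uses it there, and gives no reason for treating these two differently. This is not detail left to a later analysis plan: a method is named, and a plan that follows the article inherits it.

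The same thought applies on a much smaller scale to the primary endpoint, where tumour size is used to balance the arms but is not mentioned in the analysis.

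**Working it through.** **Voice and swallowing scores**

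The article gives no sample size or target difference for these scores, so there is no stated figure to reproduce. Inputs:
- n = 299 per arm, from Determination of sample size. That is the primary-analysis target; the number with usable questionnaires may be lower.
- Two-sided 5% test, assumed.
- Baseline to follow-up correlation r = 0.3, 0.5, 0.7, assumed.
- True difference of 0.2 SD, assumed for illustration.

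Formulas, in SD units:
- Residual variance after adjustment = 1 − r².
- Standard error = √(1 − r²) × √(2/299), where √(2/299) = 0.0818.
- Difference detectable with 80% power = (1.960 + 0.842) × standard error.
- Power = Φ(0.2/standard error − 1.960).

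Unadjusted: detectable difference 2.802 × 0.0818 = 0.229 SD; power Φ(2.445 − 1.960) = 68.6%.

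| r | Variance removed | Detectable difference | Power at 0.2 SD |
|---|---|---|---|
| none used | 0% | 0.229 SD | 68.6% |
| 0.3 | 9% | 0.219 SD | 72.7% |
| 0.5 | 25% | 0.198 SD | 80.6% |
| 0.7 | 49% | 0.164 SD | 92.8% |

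At r = 0.2 the gain is 4% of variance and power is 70.4%.

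**Primary endpoint (the optional part)**

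The stated size is 299 per group for a 5-point margin, one-sided alpha 0.025 and 80% power. With the same remission rate p in both arms, n = 2p(1 − p)(1.960 + 0.842)²/0.05². At p = 0.95 this is 2 × 0.0475 × 7.849/0.0025 = 298.3, so 299: the stated figure is reproduced. The 95% is an assumption, since the article declares no design rate. Its two background rates give other sizes (94%: 355 per group; 90.2%: 556 per group).

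Stratifying by tumour size removes w(1 − w) × gap² from the variance p(1 − p). Here w is the cT2 share and gap is the difference in remission rate between cT1b and cT2. Neither is in the article; w = 0.5 is assumed.

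| Assumed gap | Variance removed | Standard error (points) | Power at 299 per arm |
|---|---|---|---|
| not stratified | 0% | 1.782 | 80.1% |
| 2 points | 0.25 × 0.0004/0.0475 = 0.2% | 1.781 | 80.2% |
| 5 points | 0.25 × 0.0025/0.0475 = 1.3% | 1.771 | 80.6% |
| 8 points | 0.25 × 0.0064/0.0475 = 3.4% | 1.752 | 81.4% |

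In simulation (200,000 runs per scenario, true difference of −5 points, one-sided 0.025), the false-positive rate was about 0.027 to 0.028 without strata and 0.028 to 0.029 with them. Leaving the stratum out does not inflate the error rate.

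**The case against.** Several points on the other side are sound.

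- **No bias.** After randomisation the unadjusted test is unbiased, and its standard error already allows for chance imbalance at baseline. A reader might infer that the planned comparison is invalid; the article does not support that.
- **Unknown gain.** The size rests on a correlation the article does not supply. Patients with preoperative recurrent nerve paralysis are not eligible, so baseline voice scores may vary little and r may be low. The formula does not carry over to the Kruskal-Wallis fallback.
- **Unclear wording.** The article does not say whether follow-up scores or changes from baseline are tested. A change score, with equal variances at both times, has relative variance 2(1 − r). This exceeds the adjusted variance 1 − r² by (1 − r)², so adjustment is at least as precise under either reading. Data management also groups VHI and SWAL-QOL with the quality-of-life questionnaires, so the mixed model could be read as covering them. The sentence that names them gives the other test, however, so the two need reconciling.
- **Importance.** A reader might infer that voice and swallowing are where thyroidectomy alone is hoped to do better. The article does not say so: its rationale names quality of life and cost-utility. These are secondary outcomes without a power claim.
- **Primary endpoint.** A reader might infer that real precision is being lost there. The article does not rule out a stratified interval, such detail is often left to an analysis plan, and the loss is close to nil.

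These objections limit the point to efficiency on secondary outcomes. They do not explain why planned baseline scores should go unused.

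**Conclusion.** The point holds as an inexpensive gain in precision, not as an error of validity. The article fixes an analysis of VHI and SWAL-QOL without baseline while planning to collect baseline values and to use them for the other questionnaires. For assumed correlations of 0.3 to 0.7, the adjusted analysis is worth 9% to 49% of variance; at the middle value it lifts power for a 0.2 SD difference from about 69% to about 81%. These figures also assume 299 usable scores per arm and apply to the Student-test branch only.

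The remedy depends on the baseline scores being obtained, so the disagreement between the two pre-surgery lists matters in its own right. Stratifying the primary difference by tumour size is consistent with the randomisation but optional: under the assumptions above it adds at most 1.3 power points, and the primary analysis stands without it.

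**What to change.** 1. Analyse VHI and SWAL-QOL with the mixed model already planned for quality of life and anxiety, with baseline score, arm, time and arm-by-time terms. Use ANCOVA on the baseline score where there is a single follow-up. Say how non-normal scores are handled within the adjusted analysis, so that the fallback does not drop baseline again.
2. Make Randomization of patients and Baseline assessment agree that both scores are completed before surgery, and make the sections agree on the follow-up times.
3. Optional: report the primary risk difference stratified by tumour size, and state how site, the other randomisation factor, is treated.

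The cost is wording and minor programming. No new data are needed beyond the baseline questionnaires already listed. If some patients were enrolled under the shorter list and lack a baseline score, the analysis should state how they are handled.

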### Health Economics Analysis

A *cost-utility analysis* will be performed to compare total thyroidectomy to total thyroidectomy with bilateral prophylactic central neck dissection. The protocol used will be similar to the one used in ESTIMABL 1 trial and recently published in the Journal of Clinical Oncology [Borget I et al 2015]. The hypothesis is that TT alone and TTT + PND may differ in terms of the number of patients in complete remission at 1 year or in the number of patients requiring treatement of complications because of recurrent laryngeal nerve injury or hypoparathyroidism.

The horizon time will depend on the results obtained on the main criteria (1 year). If the study confirms the non-inferiority of TT versus TT + PND in terms of oncologic events, a horizon time of 1 year following the initial surgery will be considered.

Consequence will be expressed in QALYs (quality-adjusted life years). Utility score will be assessed using the EQ-5D questionnaire at baseline, 1, 3, and 5 years. QALY will be calculated by multiplying the length of time between two questionnaires by utility score.

Costs will be evaluated from the French collective perspective. Resources consumed by the patient’s management in each strategy will be collected prospectively at baseline, 1, 3, and 5 years.

#### Data collection

Resource consumption collected will concern the following direct medical costs for :Hospitalization for initial surgery, including the time in the operating room and for performing the surgeryHospitalization for the management of complicationsHospitalization for further treatments (surgery, radioactive iodine)Equipment, consultations, medical or paramedical acts for management of complicationsOther direct or indirect costs that are not expected to differ between strategies will not be collected.

#### Cost valuation

Hospital stays (whatever the cause) will be valued using the French DRGs tariffs. Outpatient care costs will be valued on the basis of pricing used by the French health insurance. Tarifs of the General Nomenclature of Professional acts (NGAP), the Common Classification of Medical Acts (CCAM) will be used. Medication will be valued on the base of pricing applied by the French health insurance.

#### Cost-utility analysis

A cost-utility analysis will be performed. One-way sensitivity analyses will be performed by varying all individual costs, incidence of events, and utility variables. Probabilistic sensitivity analyses will be performed using bootstrap resampling to estimate the uncertainty around the incremental cost-utility ratio.

### Interim analyses

No interim analysis has been planned for this study.

### Methods for additional analyses (e.g., subgroup analyses)

No subgroup analysis has been planned.

### Methods in analysis to handle protocol non-adherence and any statistical methods to handle missing data

Since the study is designed as a non-inferiority study, the primary analysis will be carried out by considering all evaluable patients (per-protocol population), as this is the most conservative approach in this context. A patient will be considered as evaluable if the treatment and the follow-up conform to the study protocol (diagnostic tests performed) and if the patient does not have detectable anti-Tg antibodies. A sensitivity analysis using the intent-to-treat (ITT) population, considering all patients in their initial group of randomization, will also be performed, to test the robustness of the results.

### Plans to give access to the full protocol, participant-level data, and statistical code

Public access of the protocol, data, and statistical code will be available at the end of the trial and after publication by contacting the principal investigator.

### Oversight and monitoring

Monitoring will be performed regularly in all participating centers, with oversight performed by the promotor.

#### Composition of the coordinating center and trial steering committee

The coordinating center is located at the promotor’s site. It is composed of the principal investigator, the methodologist and statistician, the promotor data manager, and the promotor study coordinator. They will meet annually and in addition whenever there are queries from participating centers. In each participating center, the site investigator and study coordinator will meet annually and in case of queries. The promotor’s clinical research committee will adjucate the end of the trial.

#### Composition of the data monitoring committee, its role and reporting structure

The promotor’s data management and monitoring team is composed of twelve data managers and their assistants employed exclusively for clinical studies. One data manager is assigned to the present study with backup from the team. The data management team at the promotor site is certified by the French National Cancer Institut (“Centre de Traitement de Données CTD, Institut National du Cancer”). This data management team is linked to the promotor and is independent from the national institution financing the study.

### Adverse event reporting and harms

An adverse event (AE) is any untoward medical occurrence in a patient that does not necessarily have a causal relationship with the study intervention/procedure (thyroidectomy, neck dissection, radioiodine, and rhTSH administration). An AE can therefore be any unfavorable or unintended sign (including an abnormal laboratory finding), symptom, or disease temporarily associated with a trial procedure.

A serious adverse event (SAE) is any untoward medical occurrence that at any dose:Is fatal (results in death)Is life-threateningRequires or prolongs inpatient hospitalization*Results in persistent or significant disability / incapacityIs a congenital anomaly / birth defectIs medically significant**

* Hospitalization is defined as an unplanned, formal inpatient admission, even if the hospitalization is a precautionary measure for continued observation. Thus hospitalization for protocol treatment, elective procedures (unless brought forward due to worsening symptoms), or social reasons are not regarded as a SAE.

** Medical judgment should be exercised in deciding whether an AE is serious in other situations. AEs that are not immediately life-threatening or do not result in death or hospitalization but may jeopardize the subject or may require intervention to prevent one of the other outcomes listed in the SAE definition above, should be considered serious.

Events exclusively related to tumor relapse / progression or treatment of tumor relapse / progressions are not considered as SAE.

Adverse events associated with surgery (thyroidectomy, neck dissection) are as follows: hematoma, postoperative bleeding, paralysis of the vocal cord, speech disorders, voice change, swallowing disorders, breathing disorders, hypocalcaemia, lymphatic leakage, wound infection, and nerve damage other than the recurrent nerve.

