## Introduction

### Background and rationale

For most cancers, the extent of metastasis to regional lymph nodes is a prognostic factor, and prophylactic treatment of lymph node basins for patients with no preoperative evidence of nodal disease (cN0) is often recommended. For differentiated thyroid cancer, however, the prognostic role of prophylactic central compartment neck dissection (PND) associated with total thyroidectomy for patients cN0 constitutes a major controversy for these tumors with an increasing incidence, but a very low mortality rate.

Those in favor of PND for whom it is a standard of care cite the low-level evidence suggestingImproved recurrence-free survival (retrospective case series), [1–3]A higher rate of recurrence in the presence of lymph node metastases (in some retrospective studies) and the usefulness of a complete staging in the neck to stratify for radioactive iodine treatment, [4, 5]The technical difficulty of performing a reintervention in the central compartment secondarily, andThe absence of increased permanent complications of PND (in experienced hands). [3]

Opponents of PND cite the low-level evidence suggestingNo effect on oncologic outcomes with PND (retrospective case series), [6, 7]The low rate of recurrence and mortality even without PND, [8]The efficacy of radioactive iodine to treat microscopic nodal metastases,A higher risk of complications (hypoparathyroidism and vocal fold paralysis) as compared to -thyroidectomy alone, [9]The feasibility of reoperation in the central compartment if needed with a relatively low risk of complications (in experienced hands), [10, 11] andAn increase in cost with PND. [12]

Despite the low-level conflicting evidence, different professional societies in several countries have published recommendations for or against the routine use of PND, with consequences for patients, physicians, and healthcare providers [13–19]. The French Society of Otolaryngology Head and Neck Surgery recommends PND [15] whereas the Francophone Association of Endocrine Surgery does not recommend it [19].

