Functional evaluation and quality of life:Immediate postoperative complications (0–4 months after surgery) (hypoparathyroidism requiring supplementation, recurrent nerve paralysis visualized on systematic laryngoscopy)Complications at 1 year: treatment for persistent hypoparathyroidism, recurrent nerve paralysis visualized on systematic laryngoscopy performed at 1 yearAt 1 year after randomization: Subjective dysphonia (measured via the Voice Handicap Index [45]), Subjective dysphagia (measured via the SWAL-QOL questionnaire [46])Complete remission at 1, 3, and 5 years after randomizationAt 1, 3, and 5 years after randomization: Quality of life [SF-36 + EQ-5D], Anxiety (State-Trait Anxiety Inventory), all questionnaires in their validated French translation:Quality of life (SF-36) [47]EQ-5D 3 Levels [48]Anxiety (State-Trait Anxiety Inventory) [49]Subjective dysphonia (measured via the Voice Handicap Index, VHI) [45]Subjective dysphagia (measured via the SWAL-QOL questionnaire) [46]

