#### Functional secondary criteria and quality of life

At 1 year after randomization (8+/−2 months after 131I administration): percent of patients with persistent hypoparathyroidism and/or persistent vocal fold paralysis; subjective dysphonia (Voice Handicap Index, VHI) and dysphagia (SWAL-QOL) (questionnaires in their validated French versions) compared between groups

The Voice Handicap Index is composed of 10 self-administered questions relating to the functional, physical, and emotional aspects of voice. A French version has been validated [45].

The SWAL-QOL questionnaire is composed of 44 questions concerning eating difficulty, eating duration, eating desire, food selection, fear, and social impact. The validated French version requires approximately 20 min to complete [46].At 1, 3, and 5 years after randomization: Quality of life (SF36 + EuroQol EQ-5D), Anxiety (State-Trait Anxiety Inventory-STAI) [47–49].

The SF-36 is the short-form health survey with 36 questions. It yields an 8-scale profile: physical functioning, physical condition, bodily pain, general health, vitality, social functioning, emotional status, mental health, and psychometrically based physical and mental health summary measures [47]. It has been shown to be sensitive for evaluating changes in quality of life in thyroid cancer patients [55]. It can be self-administered in 5–10 min with a high degree of acceptability. The version used in the present study is the version which has a recall period of 1 week. This questionnaire has been employed in a previously published randomized controlled trial on thyroid cancer [40, 55].

EuroQol EQ-5D consists of 5 questions (each with 3 levels of responses) and a self-evaluation of health on a visual analog scale (0–100) [48]. It is employed for the calculation of the utility score for the calculation of QALY (quality-adjusted life years) in cost-utility analysis.

Anxiety will be measured using the Spielberger STAI questionnaire [49]. The STAI state is an instrument for measurement of anxiety. It has 20 questions with four possible responses to each question. Higher scores correspond to higher levels of anxiety. It is suitable for self-administration.

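### Nerve and parathyroid injury from a reoperation after the 1-year visit enters neither SAE reporting nor any planned between-arm complication comparison, although retreatment is compared to 5 years

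*Protocol article*

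**What the plan says.** Four parts of the protocol article bear on this point.

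- **Recording of nerve and parathyroid harm.** The Follow-up section lists "Immediate postoperative complications (0–4 months after surgery) (hypoparathyroidism requiring supplementation, recurrent nerve paralysis visualized on systematic laryngoscopy" and then "Complications at 1 year: treatment for persistent hypoparathyroidism, recurrent nerve paralysis visualized on systematic laryngoscopy". No laryngoscopy or hypoparathyroidism assessment is listed after that, although patients are followed for up to 5 years (Provisions for post-trial care).
- **Comparison of that harm.** Functional secondary criteria and quality of life defines the endpoint at 1 year as "percent of patients with persistent hypoparathyroidism and/or persistent vocal fold paralysis". The statistical section agrees: the "rate of patients at 1 year with persistent hypoparathyroidism requiring medication and/or with persistent vocal fold paralysis will be compared between groups".
- **Retreatment.** Oncologic secondary criteria counts further surgery or a second therapeutic 131I at 1, 3 and 5 years, with the number and indication of each. The statistical section compares these rates at the same times and gives as one expected figure "Difference in rate of retreatment = 8.2% at 5 years".
- **SAE reporting.** Adverse event reporting and harms states: "Events exclusively related to tumor relapse / progression or treatment of tumor relapse / progressions are not considered as SAE". SAEs arising more than 30 days after the last study procedure are to be declared only when judged related to the study treatment or the research.

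**The concern.** The two strategies may place their central-neck morbidity at different times. Dissection carries its risk at the initial operation, where the 0–4 month and 1-year assessments and the SAE rules can see it. Omitting dissection may defer some risk to a later reoperation. The Background makes this part of the dispute: supporters of dissection cite "The technical difficulty of performing a reintervention in the central compartment secondarily", and opponents answer that reoperation is feasible at relatively low risk in experienced hands.

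The trial is meant to inform that dispute, and the rationale for comparators says dissection could be abandoned if non-inferiority is shown. As written, the trial will report how many patients were reoperated to 5 years, but not how many of those reoperated after the 1-year visit were left with a nerve or parathyroid deficit. At stake is the completeness of the harm comparison. The primary endpoint, remission at 1 year, is not affected.

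**Working it through.** The plan states no figure for this quantity, so there is none to reproduce. The check sets the rules side by side and then gives a range for the size.

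**Step 1. What is captured, and when**

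| Item | 0–4 months | 1 year | 3 years | 5 years |
|---|---|---|---|---|
| Hypoparathyroidism, vocal fold paralysis: recorded | yes | yes | not listed | not listed |
| Same: compared between arms | no | yes | no | no |
| Retreatment: compared between arms | – | yes | yes | yes |

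**Step 2. Can such an event enter as an SAE?** Take a patient reoperated for relapse at 2 years who is left with a vocal fold paralysis. If the paralysis is due exclusively to that operation, the exclusion removes its SAE status. The late rule requires an SAE related to the study treatment or the research, so it does not restore the event. An injury partly due to the initial operation is not exclusively due to relapse treatment and would remain reportable.

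**Step 3. Can it enter elsewhere?**
- All adverse events are to be graded by Clavien-Dindo, but the statistical section plans no between-arm comparison of adverse events beyond the 1-year nerve and parathyroid rate.
- Follow-up lists the voice (VHI) and swallowing (SWAL-QOL) questionnaires at 1, 3 and 5 years, although the functional criteria section places them at 1 year. They measure symptoms, and neither establishes hypoparathyroidism or paralysis.
- Admissions and care for these complications are collected at 1, 3 and 5 years as resource use. If non-inferiority is shown, the cost-utility horizon becomes 1 year, and the later data leave that result.

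**Step 4. Size**

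Inputs from the document: 299 patients per arm (Determination of sample size); retreatment difference of 8.2 points at 5 years and structural recurrence of 1.4% at 8 years (statistical section); recurrence contrasts from randomised evidence in Table 1 of 2.5% vs 2.7%, 3.3% vs 3.9% and 7.5% vs 8.0%.

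Assumed, because the document gives no figure: 50–100% of retreatments are reoperations, and 5–20% of reoperations leave a lasting nerve or parathyroid deficit.

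Formula: patients missed = n × difference × share reoperated × risk of a lasting deficit.

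- *From the retreatment difference:* 299 × 0.082 = 24.5 extra retreated patients. Low: 24.5 × 0.5 × 0.05 = 0.6. High: 24.5 × 1.0 × 0.20 = 4.9. As a share of 299, this is 0.2 to 1.6 percentage points.
- *From the structural recurrence level:* 299 × 0.014 = 4.2 patients in total. If all are reoperated, 4.2 × 0.05 to 4.2 × 0.20 = 0.2 to 0.8 patients.
- *From the randomised contrasts:* 299 × 0.002 = 0.6, 299 × 0.006 = 1.8 and 299 × 0.005 = 1.5 extra recurrences. If all are reoperated, 0.6 × 0.05 to 1.8 × 0.20 = 0.03 to 0.4 patients.

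The 8.2-point figure runs from time zero and, under this trial's definition, retreatment includes a second 131I. Deficits from reoperation before the 1-year visit are already counted there. The upper end is therefore generous.

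**The case against.** The strongest case on the other side has four parts.

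1. **These harms are not ignored.** They are recorded twice, a reoperation before the 1-year visit is covered by that visit, retreatment is compared to 5 years, and quality of life and complication resource use are collected to 5 years. This stands. The gap is confined to injury arising after the 1-year visit, and to its direct comparison by arm.

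2. **The SAE exclusion is a reporting rule.** No between-arm SAE comparison is described, so changing the exclusion alone would leave the 1-year harm test as it is. This also stands, and is why the fix needs two parts. The exclusion still matters for safety reporting, including the annual safety report.

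3. **The direction is not established.** A reader might infer that the missing harm falls mainly on thyroidectomy alone and that the harm comparison is biased in its favour. The documents do not support that. The 8.2-point difference comes from retrospective series. The statistical section does not say which arm has the higher rate; the direction is inferred because the Background cites the same source for dissection. The article says most of the highest-level studies show no recurrence difference, and the randomised trials in Table 1 show none.

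4. **The full protocol and the assessment timeline figure are not at hand.** They may show later data capture. That could soften the recording gap, but the article's own text fixes the comparison at 1 year and states the exclusion without qualification.

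**Conclusion.** The point holds in a limited form. Followed as written, the plan counts late reoperations by arm but neither reports as SAEs nor compares by arm the nerve or parathyroid injury that they alone cause after the 1-year visit. The remaining sources see it only indirectly.

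The size is probably small: at most about 5 patients among 299 in one arm (1.6 points), if the retrospective retreatment difference applies, every retreatment is a reoperation and 20% leave a lasting deficit. It is near zero if the randomised contrasts are the better guide. These risks are assumptions, so the range is only an indication of scale. It would be too strong to say that late harm is left out altogether or that the comparison is shown to be one-sided. Whether late harm is small in both arms is something the trial could show directly at little cost. This is a worthwhile improvement to the harm comparison and no threat to the primary conclusion.

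**What to change.** - **Adverse event reporting and harms:** limit the exclusion to the relapse or progression itself, and state that complications of its treatment are reported as SAEs when they meet a seriousness criterion.
- **Follow-up, functional secondary criteria and statistical methods:** add a comparison by randomised arm at 3 and 5 years of hypoparathyroidism still requiring supplementation and of known persistent vocal fold paralysis, both including deficits after retreatment. Record both in the same way for every patient in both arms at the existing yearly visits.
- **Laryngoscopy obtained only around a reoperation:** report these results separately. Merging them into the main comparison would make detection depend on retreatment status and could introduce a bias of its own.

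The cost is a protocol amendment, a few eCRF fields and a few more SAE forms. One limit remains: without systematic laryngoscopy after 1 year, vocal fold paralysis may be under-detected, and the report should say so.
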